### Sample size

Based on pilot data, systolic BP is expected have a standard deviation of 20 mmHg. A clinically important difference in systolic BP is estimated to be 7 mmHg; this is a difference often seen with initiation of treatment and is associated with reduction in cardiovascular risk [49]. To have 80% power to find a difference in systolic BP of 7 mmHg using a two-sided unpaired t-test with α = 0.05 would require 258 total patients. To account for clustering, this sample size must be multiplied by a variance inflation factor (VIF) = [1 + (n - 1) × ICC], where n is the mean cluster sample size and ICC is the intra-class correlation coefficient, a measure of the degree of correlation within clusters [50]. From baseline data, the mean cluster size (number of patients with diabetes and/or IHD in each practice) is approximately 328. Using a presumed ICC of 0.05 (based on ICCs seen in the literature[51]), the VIF equals 17.4. Thus, 4,489 patients with diabetes and/or IHD are required to find a difference of 7 mmHg in BP, which equates to 13.7 clusters.

For LDL values, pilot data show a standard deviation of 0.90. Therefore, using the same calculations, the trial will have power to show an absolute difference in LDL of 0.32 mmol/L; this difference has been shown to be associated with reduction in cardiovascular risk [52]. This type of small improvement in the management of these very common chronic diseases could translate into a large impact on the population scale.

Based on pilot data, the standard deviation for the composite process primary outcome is expected to be 1.61. For this outcome, pilot data were also used to find that the ICC was 0.0059, but to be conservative this can be rounded up to 0.01, giving a VIF of 4.28. Therefore, to show an absolute difference in the final composite process score of 0.3 (effect size 0.19), a sample size of 3,878 patients would be needed, which equates to 11.82 clusters.

Most of the power in cluster-trials comes from the number of clusters, rather than the number of patients. Therefore, dropout of a few participating physicians (or many of their patients) would only minimally decrease power. We do not expect dropout of entire clinics; clinic managers are committed to this project and have facilitated the recruitment of individual physicians at each clinic. However, even with a loss of two of the fourteen clinics, the same calculations indicate that we would have 80% power to find differences of 8 mmHG BP or 0.36 mmol/L LDL.

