**Analysis:**

Intention-to-treat approach will be used to analyze the trial. Analysis will be performed on patient-level variables using generalized estimating equation models to adjust for covariates and account for the clustered nature of the data. The trial is powered to show small, but clinically important differences of 7 mmHG in systolic BP and 0.32 mmol/L in LDL.

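### With 14 practices, a test on 12 degrees of freedom has about 74% power for 7 mmHg and 76% for 0.32 mmol/L rather than 80%, and the figures for losing two clinics do not follow from the stated method

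*Protocol article*

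**What the plan says.** The Sample size section of the protocol article takes these steps:

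- For blood pressure, "systolic BP is expected have a standard deviation of 20 mmHg". The target is set as "To have 80% power to find a difference in systolic BP of 7 mmHg", which "using a two-sided unpaired t-test with α = 0.05 would require 258 total patients".
- That number is multiplied by a variance inflation factor (VIF) of 17.4, from an ICC of 0.05 and a mean of 328 patients per practice. The result is "4,489 patients with diabetes and/or IHD are required to find a difference of 7 mmHg in BP, which equates to 13.7 clusters".
- For LDL, "For LDL values, pilot data show a standard deviation of 0.90", and by the same route "the trial will have power to show an absolute difference in LDL of 0.32 mmol/L".
- The last paragraph of the section considers losing two of the fourteen clinics and says "the same calculations indicate that we would have 80% power to find differences of 8 mmHG BP or 0.36 mmol/L LDL".

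The Analysis paragraph of the abstract carries the result forward: "The trial is powered to show small, but clinically important differences of 7 mmHG in systolic BP and 0.32 mmol/L in LDL".

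**The concern.** Practices are allocated, so the treatment comparison is between practices. The VIF enlarges the variance correctly for this. It does not change the reference distribution, which stays that of a test with about 256 df (critical value about 1.96). Seven practices against seven leave 12 df (critical value 2.18). The article itself says, in the last paragraph of the Sample size section, that the number of clusters supplies most of the power, but no step in the calculation reflects how few there are. There is little reserve to absorb the difference: 13.7 clusters are required and 14 are available.

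At stake is how a null result on two of the three primary outcomes would be read. It would seem to count against 7 mmHg and 0.32 mmol/L with 80% power when the 14 practices give somewhat less. The two-clinic figures raise a separate question, because they are attributed to a calculation that does not produce them.

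**Working it through.** **Inputs.** From the Sample size section: SD 20 mmHg and 0.90 mmol/L, two-sided α 0.05, 80% power, ICC 0.05, mean cluster size m = 328. From Table 1: 14 practices and 4,593 patients (4,593/14 = 328). The allocation ratio is not stated, so equal arms are assumed.

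**1. The plan's own figure.** Detecting 7 mmHg with SD 20 needs 129 per arm, or 258 in total. VIF = 1 + 327 × 0.05 = 17.35, rounded to 17.4. Then 258 × 17.4 = 4,489, and 4,489/328 = 13.7 clusters. For 0.32 mmol/L, 250 × 17.35 = 4,338 patients, or 13.2 clusters. Both reproduce.

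**2. Fourteen practices, 7 v 7.** SE = SD × √[(VIF/m) × (1/7 + 1/7)].

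- BP: 20 × √(0.0529 × 0.2857) = 2.459, and 7/2.459 = 2.847.
- LDL: 0.90 × √(0.0529 × 0.2857) = 0.1106, and 0.32/0.1106 = 2.892.

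| | Normal reference (VIF method) | Noncentral t, 12 df |
|---|---|---|
| Power, 7 mmHg | 81.2% | 74.3% |
| Power, 0.32 mmol/L | 82.4% | 75.7% |
| Detectable at 80%, BP | 6.89 mmHg | 7.51 mmHg |
| Detectable at 80%, LDL | 0.310 mmol/L | 0.338 mmol/L |

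A simulation of 200,000 trials of practice means gave 74.5% for 7 mmHg.

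**3. More practices (t on K − 2 df).** With 16 practices, power is 80.8% for 7 mmHg and 82.0% for 0.32 mmol/L. With 18 it is 85.8% and 86.8%, and with 21 it is 91.1% and 91.9%.

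**4. Twelve practices, 6 v 6.** SE = 20 × √(0.0529 × 0.3333) = 2.656 mmHg, and 0.1195 mmol/L for LDL.

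- Stated method: (1.960 + 0.842) × 2.656 = 7.44 mmHg, and 2.802 × 0.1195 = 0.335 mmol/L. A 7 v 5 split gives 7.55 and 0.340. Neither gives 8 and 0.36.
- Both stated values equal 0.40 SD (8/20 and 0.36/0.90). By the stated method, 0.40 SD is the detectable difference at about 10.4 clinics, not 12.
- Power at 8 mmHg and 0.36 mmol/L with 12 clinics is 85.4% by the stated method and 77.5% on 10 df.
- On 10 df the detectable differences are 8.26 mmHg and 0.372 mmol/L.

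**5. Composite process score.** With SD 1.61, ICC 0.01, 14 practices and 12 df, power for a difference of 0.3 is 80.1%, so its 80% claim stands at 14 practices.

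**The case against.** The strongest reply has four parts.

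- **Enrolment is still open.** Table 1 describes the initial 14 clinics, Participants and data collection allows growth of up to 50%, and Allocation and blinding keeps enrolment open for up to six months. Sixteen practices suffice. This stands as a limit on the point: the 74% to 76% holds only if enrolment stops at 14. But the growth is only possible, and neither the sample size calculation nor the two-clinic scenario uses it.
- **Baseline adjustment is planned.** The Analysis section adjusts for baseline BP and LDL. Since (7/7.51)² = 0.87, a variance reduction of about 13% would restore 80% on 12 df. An ICC of about 0.043 in place of the presumed 0.05 would do the same. Both are plausible, but the article gives no figure for the gain, and its calculation takes no credit for it. Practice-level covariates could also use up df, so quoting the loss without the gain would be one-sided.
- **The arithmetic is right.** It is. A reader might infer that 4,489 or 13.7 is miscalculated. Both reproduce, and the fault lies in the reference distribution.
- **The two-clinic figures are cautious.** By the stated method they are, with about 85% power against the 80% claimed. A reader might infer that the reassurance about dropout collapses. It does not: on 10 df the shortfall is 2.5 percentage points.

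Unequal practice sizes work in the other direction. Table 1 gives a median of 263 and an IQR of 219 to 505 against the mean of 328 used. Purely as an illustration, assumed coefficients of variation of 0.3 and 0.5 in VIF = 1 + [(1 + CV²)m − 1] × ICC give 71% and 65% for 7 mmHg. The article gives neither the individual sizes nor the working correlation, and a weighting that allows for clustering would lose less. Only the direction can be relied on.

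**Conclusion.** The point holds, with moderate importance. Under the article's inputs, a 7 v 7 split, equal practice sizes and no gain from baseline adjustment, 14 practices give about 74% power for 7 mmHg and 76% for 0.32 mmol/L. That is about 6 and 4 points below the stated 80%. The detectable differences move from 7 to about 7.5 mmHg and from 0.32 to about 0.34 mmol/L. The figures for two lost clinics do not follow from the calculation to which they are attributed: they are too large by that method and slightly too small on 10 df.

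Two stronger readings are not supported. One is that the trial is underpowered whatever happens, which ignores possible growth and baseline adjustment. The other is that the differences cannot be called small because nearly every patient would have to start treatment. The article says only that 7 mmHg is commonly seen when treatment is started, and it does not exclude other routes to an average change.

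**What to change.** In the Analysis paragraph of the abstract and in the Sample size section, restate the BP and LDL power using a t reference with (practices − 2) df. For 14 practices, give either about 74% and 76% power at 7 mmHg and 0.32 mmol/L, or 80% power at about 7.5 mmHg and 0.34 mmol/L.

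In the two-clinic sentence, replace 8 and 0.36 with about 8.3 mmHg and 0.37 mmol/L on 10 df. If the large-sample formula is kept, give about 7.4 mmHg and 0.335 mmol/L and say that it makes no allowance for the number of practices.

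State the assumptions: equal arms, ICC 0.05, equal practice sizes and no credit for baseline adjustment. Recalculate when the six-month enrolment window closes, using the actual number and sizes of practices.

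The cost is text only. No extra enrolment and no change to conduct or analysis is needed; the drawback is slightly less favourable stated figures.

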### Qualitative analysis and process evaluation

Previous qualitative studies have isolated timeliness, customizability, and a non-punitive tone as key criteria for 'actionable' feedback [53]. Evidence from the organizational literature suggests that the recipient must be satisfied with the feedback for it to be accepted and acted upon [54]. Unfortunately, the literature has not provided clear direction regarding how to design feedback interventions targeted at family physicians to accomplish this goal.

One previous study has assessed eight Ontarian physicians' reactions to a 20-minute one-on-one performance assessment presentation based on chart audits and patient questionnaires, and found that physicians welcomed it [55]. Even though the data were garnered directly from charts, the participants expressed concerns about government involvement in the performance improvement process. Another study revealed a general scepticism amongst physicians regarding quality improvement interventions based on secondary databases [56]. Nevertheless, the MOHLTC, is now using administrative data to send all family physicians 'Diabetes Testing Reports' regarding their patients with diabetes [57]. These reports from the government will provide far less data to the physicians (and nothing regarding patients with IHD) compared to the intervention described in this protocol. This context provides an opportunity to work with physicians receiving two types of diabetes feedback to explore the barriers and facilitators to Ontario family physicians' acceptance and utilization of performance feedback, and to examine the perceived actionability of various approaches to the design and delivery of feedback. While the ongoing government feedback will likely enrich the qualitative component of the study, we do not believe that it will impact the inferences made from the trial. All participants will receive the government feedback, but the government feedback does not explicitly encourage goal setting or action plans.

Semi-structured, individual interviews will be conducted using an interview guide, developed based on a review of the literature and consideration of the twelve domains described by Michie *et al*. to explain behaviour change in response to an intervention [58]. We will use 'stratified purposeful sampling' [59]; we will select participants with those features believed to be relevant, not with the goal of probabilistic representativeness, but for informational representativeness. For instance, guideline adherence and quality of care may be inversely related to years in practice [60] and physician gender [61], so variety will be sought in these factors. Additionally, the participants will be chosen to represent varying levels of baseline performance, because this was found to be an important predictor in the Cochrane review. It is expected that saturation may be accomplished with approximately 12 interviews [62]. The sample will be weighted with about two-thirds of participants having received the enhanced feedback. To account for time away from patient care, an honorarium will be offered for participation.

Interviews will be recorded and a transcription service used to produce verbatim electronic transcripts. These will be stored with encryption software on a password-protected computer drive. Identifying factors will be omitted. NVivo™ software will be used to assist with the data analysis. The framework analysis approach, as described Ritchie and Spencer [63] (and more succinctly by Pope *et al*.[64]) aims to accurately reflect the original accounts of the participants through the use of inductive techniques, yet start out deductively with preset goals. As such, it represents an ideal foundation for analyzing qualitative data within a pragmatic, mixed methods study such as this one. For example, it has been successfully used in the past as part of a mixed method study investigating barriers and facilitators to guideline uptake in the ICU [65].

The identification of themes will be tracked along with dates of interpretations to provide an audit trail documenting the analysis. This is one way that trustworthiness in the results can be increased [66]. Next, an index of themes will be developed by combining *a priori *objectives and issues identified in the literature with those raised by the participants and recognized through the readings. This process will occur after seven interviews have been completed and will be repeated in part by a second researcher (JB). It is thought that multiple coding provides a system of check and balances to ensure that all possible themes are given consideration [67]. Disagreements will be settled through consensus and this process may lead to changes in the interview guide. At this point, disconfirming evidence to ensure saturation of themes will be sought from further participants through the use of snowball sampling (by asking participants to suggest colleagues that may have unique perspectives on feedback). In this way, elements of multiple coding and the constant comparative method will be incorporated. Therefore, the qualitative protocol will meet the criteria described by Kuper for judging qualitative research [68].

## Discussion

With the use of audit and feedback interventions likely to increase over time, there is a need to understand how their design effects the behaviour of primary care providers. This project will play a role in learning how to generate feedback reports that are useful for family physicians. Even if the trial is negative, the qualitative process evaluation will provide useful information and generate new study questions. Future studies may then compare the cost-effectiveness of using interventions similar to the one described in this trial against more intensive interventions such as academic detailing or practice facilitators.

There are also some important limitations that warrant discussion. One concern regarding generalizability is that it is possible that there will be a specific interaction between the worksheet intervention and the feedback such that adding the worksheet to other designs/types of feedback or other interventions may not work as well. It is also important to note that participants in EMRALD are a convenience sample of Ontario family physicians using Practice Solutions^®^. Therefore, findings from this group will not be strictly generalizable to other providers who use different EMR systems, or to those not using EMR at all. In addition, many of the clinics are involved in other quality improvement interventions. Thus, these clinics may be more innovative and may also be achieving a higher level of evidence-based care than most other primary care providers.

Perceived data accuracy has been identified as an essential feature for acceptance of feedback reports [69], and previous studies have shown that data quality from EMRs are uncertain [70]. While we have validated algorithms for identifying patients who have diabetes and/or IHD in this database, the automated chart audits that are the basis for both the intervention and the outcome assessment may occasionally have errors. However, there is no reason to believe that any such errors occurring in the data abstraction process represent a risk for bias; any problems with the algorithm would be equally likely to occur in either arm of the trial.

This is a pragmatic trial that is powered to find small (but important) effects of a feedback intervention based on the addition of a theoretically-informed worksheet. While a longer, larger trial would be ideal to assess true cardiovascular endpoints, the size and timeframe of this trial have been designed to ensure feasibility. Psychological theory applicable to feedback interventions indicates that the worksheet intervention tested in this trial should help family physicians to close the gap between their intended and actual behaviours with respect to the care they provide for their patients. If the intervention works in this sample, it could be tested more broadly; if it is not effective, it may be necessary to try more intensive approaches to facilitate providers to achieve their quality improvement targets.

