### Participants and data collection

Through the Electronic Medical Record Administrative data Linked Database (EMRALD), family physicians from all regions of Ontario who have been using Practice Solutions^® ^Electronic Medical Records (EMRs) for at least 12 months have signed a data-sharing agreement with the Institute for Clinical Evaluative Sciences (ICES) where EMRALD is held. ICES is a prescribed entity, under the province of Ontario's Personal Health Information Protection Act, which allows for the collection of individual level health information for use in planning and managing the healthcare system.

At ICES, mechanisms to extract, securely transfer, and de-identify the EMR data have been established[25]. For patient visits, consultations, investigations, and treatments, data in EMRALD compare well with (and often out-perform) administrative databases [unpublished data]. Furthermore, algorithms to identify patients in the EMRALD database with diabetes (sensitivity 83.1%, specificity 98.2%) [26] and IHD (sensitivity 72.4%, specificity 99.6%) [27] have been validated. Since publishing those papers, we have made further improvement to the diabetes algorithm (by considering the 'problem list' and 'past medical history' fields in addition to the lab tests and prescriptions) resulting in a sensitivity of 90.9% and specificity of 99.2%. The algorithm for identification of the IHD algorithm has also been improved by continuing to refine the search terms used to identify patients in the 'problem-list' and 'past medical history' fields. The algorithms developed for EMRALD do not require any special coding or data input by the participating physicians.

Family physicians were originally invited to participate in EMRALD through convenience sampling of EMR users. Presently, all participants work in multi-provider clinics and nearly all have access to allied healthcare providers. As a result, participants are not necessarily representative of all Ontario family physicians or of all primary care EMR users. However, this concern is partially mitigated by the varied characteristics of physicians in the sample (Table 1). As EMRALD continues to recruit new family physicians, the diversity of the sample is expected to grow. The number of participating physicians and practices in EMRALD may grow by as much as 50% during the first six months of this trial.

**Table 1 T1:** Characteristics of initial 14 clinics and 54 family physicians in the trial

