**Physicians per clinic, n (%)**					

1 to 2	5 (35.7%)			**Years using EMR, n (%)**	

3 to 5	4 (28.6%)			Less than 3	5 (9.3%)

6 to 11	5 (35.7%)			3 to 6	45 (83.3%)

				More than 6	4 (7.4%)

N, n = number, IHD = ischemic heart disease, EMR = electronic medical record

For the present study, all EMRALD participants were sent consent forms and invitations to participate. Minimal eligibility criteria are applied. Physicians with less than one year of experience with EMR or with less than 100 rostered, active adult patients will be excluded, because these 'new' physicians would not have adequate data to assess some of the quality indicators. To be considered active, and to ensure there is a history with the physician, patients must have at least one visit between 12 and 36 months prior to the data upload date. The EMR data for all remaining physicians are assessed to ensure completeness with respect to electronic capture of lab tests and prescriptions. Finally, because ICES does not permit reporting of cells smaller than five (to ensure confidentiality), the data for the remaining physicians are assessed to ensure that each has more than five patients with diabetes and more than five with IHD.

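### The reason given for equal identification errors in both arms is unsound, because the diabetes algorithm reads tests and prescriptions that the worksheet aims to change

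*Protocol article*

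**What the plan says.** - **Discussion.** The article acknowledges that "the automated chart audits that are the basis for both the intervention and the outcome assessment may occasionally have errors". It then sees no reason to suspect bias, because "any problems with the algorithm would be equally likely to occur in either arm of the trial".
- **Participants and data collection, algorithms.** The diabetes algorithm was improved "by considering the 'problem list' and 'past medical history' fields in addition to the lab tests and prescriptions". Its stated accuracy is now 90.9% (sensitivity) and 99.2% (specificity). The IHD algorithm was improved by "continuing to refine the search terms used to identify patients in the 'problem-list' and 'past medical history' fields"; tests and prescriptions are not mentioned for it.
- **Participants and data collection, eligibility text after Table 1.** To count as active, "patients must have at least one visit between 12 and 36 months prior to the data upload date".
- **Timeline.** Practices upload data every six months, and the final analysis follows an audit at 24 months.
- **Outcomes and Table 2.** The primary process outcome counts tests done and prescriptions held. Which items count depends on whether the patient is labelled as having diabetes, IHD or both. With both labels, seven items are scored and the sum is multiplied by 6/7.
- **Analysis.** The primary analysis pools all patients with either condition. Subgroups are formed by disease label.
- **Allocation and blinding.** Minimization used each practice's baseline outcome data and its number of patients with diabetes and/or IHD. The audit and the statistical analysis are blinded to arm.

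**The concern.** The dismissal of bias rests on the algorithm being the same in both arms. A fixed rule gives equal error rates only if what it reads is unaffected by allocation. Here the rule for diabetes reads laboratory and prescription records, and the trial's hypothesis is that the worksheet changes what physicians do, including what they test and prescribe. If the worksheet works, even partly, those records will differ by arm. The chance that a patient is identified as having diabetes may then differ too.

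Two things could follow. Patients could enter the analysed set in one arm who would not have entered in the other. Patients already in the set as IHD-only could be moved to the group with both conditions, which changes the items on which they are scored and the subgroup to which they belong. Either would compare groups shaped by events after allocation, which minimization at baseline cannot balance. The composite process score is the most exposed outcome, because its definition depends on the label.

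**Working it through.** **1. The plan's own yardstick.** Inputs from Sample size: target difference 0.3 points, SD 1.61, 80% power, two-sided α = 0.05, inflation factor 4.28, mean cluster size 328.
- Per arm: 2 × (1.96 + 0.84)² × 1.61² / 0.3² ≈ 452, or 453 with the t correction; total 906.
- 906 × 4.28 = 3,878 patients, and 3,878 / 328 = 11.82 clusters.

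Both match the article. The 0.3 points is the scale for what follows.

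**2. Does the algorithm read what the worksheet targets?**
- The diabetes algorithm reads problem list, past history, laboratory tests and prescriptions.
- The process score counts A1C, ACR, LDL and, in IHD-only patients, fasting glucose; and prescriptions for a statin, an angiotensin-modifying agent and, with IHD, aspirin.

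The two share field types. The article does not list which tests or drugs trigger the diabetes label. I assume that glucose-related results are among them. On that assumption the most direct route is fasting glucose testing in IHD-only patients, which the score rewards.

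**3. The visit window, if the rule is applied at the 24-month upload.** Take allocation as month 0.
- Earliest qualifying visit: 24 − 36 = month −12.
- Latest qualifying visit: 24 − 12 = month +12.

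Of the 24-month window, 12 months (half) lie after allocation.

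**4. What relabelling does to one patient's score.** Let c be the number met of the five items common to both labels (BP, LDL, aspirin, statin, angiotensin-modifying agent). Let F, A and U be 1 if fasting glucose, A1C and ACR were done, and 0 if not.
- IHD-only score = c + F.
- Both conditions = (c + A + U) × 6/7.

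| Patient | As IHD-only | As both | Change |
|---|---|---|---|
| c = 5, F = 1; ACR missing | 6 | 6 × 6/7 = 5.14 | −0.86 |
| c = 5, F = 1; A1C and ACR missing | 6 | 5 × 6/7 = 4.29 | −1.71 |
| c = 5, F = 1; none missing | 6 | 7 × 6/7 = 6 | 0 |
| c = 3, F = 1; A1C and ACR done | 4 | 5 × 6/7 = 4.29 | +0.29 |

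The first two changes are larger than the 0.3 target, but they apply to one patient, not to an arm mean. The last row shows that the sign is not fixed.

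**5. From one patient to an arm mean (shares assumed; the article gives none).** If a share p of one arm were relabelled at a loss of 0.86 to 1.71 points each:
- p = 1%: 0.01 to 0.02 points, or 3% to 6% of 0.3.
- p = 5%: 0.04 to 0.09 points, or 14% to 29% of 0.3.

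**6. Newly added patients (assumed).** Suppose a share of one arm was identified only through activity after allocation, and that these patients differed from the rest by 1 to 3 composite points in either direction. Stated sensitivity leaves 100 − 90.9 = 9.1% of true diabetes cases missed, so 9.1% is close to a ceiling for finding missed cases.

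| Share | Composite shift (target 0.3) | Systolic BP shift if they differ by 5 to 10 mmHg (target 7) |
|---|---|---|
| 1% | 0.01 to 0.03 | 0.05 to 0.1 mmHg |
| 5% | 0.05 to 0.15 | 0.25 to 0.5 mmHg |
| 9.1% | 0.09 to 0.27 | about 0.5 to 0.9 mmHg |

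**The case against.** The best defence is that the premise of re-identification is not stated. The active-patient rule refers to a single upload date and sits among the enrolment criteria. The six-monthly uploads are described as serving the feedback reports. Figure 2, on patient flow, is not shown and may define a baseline cohort, and an article may leave the analysis set to the full protocol. This stands: a reader might infer that eligibility is re-applied at every upload, but the text does not say so. It does not rescue the Discussion sentence, which argues from the algorithm's behaviour and not from a fixed cohort.

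The mechanism is also narrow. Both arms receive the same reports and handout. More testing of patients already identified adds nobody. The route through tests and prescriptions applies, as described, only to the diabetes label. IHD patients found to have diabetes are already in the pooled analysis. All of this is fair. It makes relabelling a clearer risk than the entry of new patients, and relabelling changes the score.

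Three stronger readings are tempting and unsupported:
- That newly found patients would be milder or less well worked up, so that the bias has a known sign. Nothing in the article says so. Patients found through a new test have had that test, and the table of score changes shows both signs.
- That the rise in sensitivity from 83.1% to 90.9% measures the likely gap between arms. It reflects added data fields. A further gain of the same ratio in one arm would mean 90.9 × 90.9 / 83.1 = 99.4% sensitivity there, almost every missed case.
- That recruitment growth is part of the problem. The statement that "The number of participating physicians and practices in EMRALD may grow by as much as 50% during the first six months" concerns enrolment, not algorithm error, and new practices are to be minimized on their own baseline data.

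**Conclusion.** The concern holds in a limited form. The reason given for excluding bias is unsound: the same blinded rule is applied in both arms, but for diabetes its inputs are of the kind that the intervention is meant to change, so identification and disease label can differ by arm. No text shown closes that route by fixing patients and labels at baseline.

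The size cannot be derived from the article. A single relabelled patient can lose 0.86 or 1.71 composite points. Under the assumed shares, the arm mean moves by anything from a negligible amount to a substantial part of the 0.3 target. Mean systolic BP would probably move by less than 1 mmHg against 7. Direction is unknown. The conclusion rests on two assumptions: that glucose-related results can trigger the diabetes label, and that patients or labels are updated after baseline. If the full protocol already fixes both at baseline, only the sentence in the Discussion needs correcting.

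**What to change.** - State that the primary analysis set, and each patient's disease group, are taken from the practice's baseline upload before that practice's allocation, and that those patients are followed to the 24-month audit. Practices that enrol later use their own baseline upload.
- Analyse patients identified later as a sensitivity analysis.
- Report by arm the number of newly identified patients and the number whose disease label changed.
- Replace the Discussion sentence with an acknowledgement that identification could differ by arm, because the diabetes algorithm reads tests and prescriptions, and say how the analysis set guards against this.

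The cost is low: baseline data, including patient counts per practice, were already drawn for minimization. Later-identified patients leave the primary analysis, and a closed cohort will lose some patients over 24 months. The loss of power should be small, since, as the Sample size section notes, power depends mainly on the number of practices.
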